**In conclusion, the study foods are therefore considered safe for the participants.**

## 7.2 Safety of study procedures

Blood samples will be taken by experienced laboratory technicians who are used to taking blood samples in children, and the only expected risk in relation to blood sampling is the risk of a mild pain and potentially a small bruise at the site of the prick, which will disappear within a few days. The volume of the blood sample is small (40 ml per sample) and the two blood samples are taken three months apart. To reduce the discomfort of blood sampling we will provide local anesthetic patches (EMLA) to the parents, containing lidocaine and prilocain, to put on both forearms at home before the blood sampling. The patches are sold over-the-counter in Danish pharmacies.

Bio impedance is non-invasive and has not been reported to give untowards events. A very small electric current is sent through the body, however it is lower than the threshold of perception and unlikely to stimulate electrically excitable tissues such as heart and cardiac muscle. The method has been approved by the US Food and Drug Administration.

The cold pressor test generally causes some cold-related pain, but this risk is balanced by the participants' control over the process (i.e., their ability to withdraw their hand if it becomes too uncomfortable) and the fact that the cold-related pain mounts fairly slowly so that it can be terminated before it becomes too uncomfortable (60). As a further means of minimizing risk, the following guidelines published by Von Baeyer and colleagues (2005) will be followed: Children with a history of cardiovascular disorder, fainting or seizures, frostbite, open cut, sore or fracture of hand to be immersed, and any history of Reynaud's phenomenon (hands get white, then blue, on

exposure to cold, then red on warming), will be excluded from the cold pressor test. In addition, the children will have breakfast before the test to reduce risk of a vasovagal stress response (fainting) (61). A review of cold pressor test studies with an estimated total of 3000 child participants only reported two adverse events involving significant but transient distress (60). In our study of 200 children we therefore consider the risk of an adverse event minimal. However, we will pay close attention to the reaction of the child, and if a child experiences severe distress or displays other symptoms, we will terminate the test, comfort the child and immediately call their parent.

The study foods and activities are not expected to cause other side-effects or harms. As in any other research projects there is a theoretical risk of unexpected events or risks, which cannot be foreseen by investigators or study participants and therefore this study cannot exclude risks which are unknown at this time. If we suspect or the participants report any side effects, harms or diseases during the study, the medically responsible physician will determine whether the study participant can continue in the study and will inform the parents/ custody holders. If we obtain new information about the procedures or intervention products that are of major relevance to the participants, the parents/ custody holders will receive written and oral information hereof and will have to give renewed written consent if they want to continue participation in the study.

## **8. BIOLOGICAL MATERIAL**

In connection with the study, a research biobank will be established for storage of biological material, that is blood (2 x 40 ml), hair samples (2 x 5-20 mg), and salivary samples (4 x 0.5-2 ml) for each child. The whole project and the research biobank are reported to the Danish Data Protection Agency via common reporting system in the Faculty of SCIENCE [fællesanmeldelse], ref. no. 2015-57-0117. Biological material stored in the research biobank will be destructed after analysis and no later than 7 years after study completion. Samples will be analyzed at NEXS and at other laboratories in Denmark, other EU countries, USA, and Canada. After shipping to these countries samples will be treated in agreement with the national laws of the recipient country. Samples will be sent in coded tubes without any accompanying data files that could potentially identify the participants.

Possible excess material of blood will, if the parents/custody holders have agreed to this, be transferred to a biobank; otherwise it will be destroyed. The biobank material will be stored at -80°C at Department of Nutrition, Exercise and Sports, [name], for max. 7 years after study completion. The material will only be used in new and related research projects after these have achieved approval by the Danish Regional Committee on Biomedical Research Ethics, unless the samples have been totally anonymised, this means that the ID-log that connects study participants and biological material is destroyed. If the parents/custody holders choose to donate possible excess material to the biobank and later on regret it, they can contact Department of Nutrition, Exercise and Sports and have their child's blood destroyed. Parents/custody holders will, according to the procedures at Department of Nutrition, Exercise and Sports, sign a separate consent form for the biobank. Parents/ custody holders will be informed that

it is completely optional if they want to donate excess material from the child to the biobank and that the decision has no consequences for the participation in the study. The applicant is aware of the fact that collection of biological material for a biobank is not covered by the committee law, but by the Danish Act on Processing of Personal Data (*Persondataloven*). As we consider the procedure relevant for the complete research protocol in Denmark, the information is included in the material for the committee.

## 9. ETHICAL ASPECTS

### 9.1 Compliance with ethical and scientific regulations and guidelines

- The study and recruitment will not be initiated until approval has been obtained from the Danish Regional Committee Biomedical Research Ethics. The written approval and potential appendices will be kept at NEXS, where the study will be conducted. If any major changes are made to the protocol or the essential appendices to the protocol, these will be submitted to the Committee as a supplementary protocol.
- We will follow the Danish Act on Processing of Personal Data [Persondataloven] for all data collected in the study. The study as a whole is reported via the common reporting system in the Faculty of SCIENCE [fællesanmeldelse], ref. no. 2015-57-0117.
- The study will be conducted in agreement with the ethical principles described in the latest, updated version of the Helsinki Declaration (62) and will be registered in the database [www.clinicaltrials.gov](http://www.clinicaltrials.gov) before recruitment is initiated.

### 9.2 Informed consent

The parents or custody holders of the child will be informed orally and in writing about the study, and have to be legally able to give written consent for the child's participation. Parents/ custody holders can withdraw their consent for participation at any time without giving explanations and without any consequences for them or the child. Parents will be informed that data, that was collected before withdrawal, may be used by the investigators in the data analysis of the study. If they do not wish this use of their data, they must tell us to delete their data from the data set. The informed consent gives all relevant authorities that regulate the study, such as the Danish National Committee on Biomedical Research Ethics, consent to see the data of the participants.

We will not perform any study activities until both parents or all custody holders have given written consent based on oral and written information on:

- The study and its activities and procedures
- Their right to withdraw from the study at any time without giving explanations and without consequences
- The procedures for collection and storage of the personal and biomedical data
- That the personal and biomedical data will be processed anonymously

### **9.3 Other information provided to the parents**

During and after the study the parents will be informed if:

- The study responsible becomes aware of any new information on effects, risks or harms related to the intervention
- The design of the study is changed substantially
- The study team members discovers any important health information about their child (unless they have specifically declined to receive such knowledge)
- The study is discontinued; in this they will be informed about the reasons for the discontinuation

If the project staff suspects that a child is ill during the information meeting or during the study or suspect any side-effects of participating in the study, the medically responsible physician will determine whether the participant can continue in the study and inform the parents/ custody holders. If the parents wish so, they will be informed about the results of these investigations.

### **9.4 Ethical considerations in relation to conducting the study**

#### **9.4.1 Study foods**

The study foods that will be used are fish and poultry such as chicken cuts, filets and products that are commercially available in Danish supermarkets and commonly eaten by Danes. Intake of 300 g/week of fatty fish is within the national dietary recommendation on fish intake (1). As described in section 7.1 we have thoroughly considered the safety aspects of children's consumption of the study foods for 12 weeks, particularly in relation to potential contaminants in the fish. Based on these calculations and the tolerable intakes of unwanted substances defined by EFSA, we conclude that the study foods are safe for the participants.

#### **9.4.2 Blood sampling**

We have thoroughly considered the ethical aspects of the discomfort of blood sampling. Since the blood samples are crucial for investigating one of the primary outcomes (triacylglycerol) and compliance (n-3 LCPUFA) and since this investigation is of major importance for qualifying or improving dietary fish recommendations for children and investigating potential cognitive, behavioral and emotional effects of fish, we consider the discomfort of the blood sample to be outweighed by its usefulness. The discomfort of blood sampling will be minimized by use of local anesthetic patches on the forearms before blood sampling. Moreover, as described in section 7.2, blood will be sampled by laboratory technicians who are experienced in blood sampling in children. The only expected risk of blood sampling is a mild pain at the site of the prick on the arm and potentially a small blue bruise at the site of the prick, which will disappear within a few days.

#### **9.4.3 Fasting**

The children will be asked to meet at the baseline and endpoint visit fasting. The cardiometabolic examinations are conducted in the morning, and the children will be served a breakfast afterwards before the cognitive tests. A fasting period of this duration is relative short, and we do not expect the children to experience considerable discomfort due to the fasting. However, if this should be the case, the examinations will be discontinued immediately and the child offered drinks and food.

#### **9.4.4 Puberty questionnaire**

As described in section 4.4 the parents will be asked to report the child's pubertal stage, aided by the child if necessary. The recording is scientifically important as pubertal onset affects body composition and a number of the blood values to be measured. The parent(s) will fill out the questionnaire at home or at the baseline visit. A member of the study team will be available for answering questions, but will not otherwise partake in this activity unless asked to, in order to assure participant privacy.

#### **9.4.5 Discomforts from other measurements**

Some children may be slightly irritated by wearing the accelerometer, but the children can take off the accelerometer if annoyed too much. Some children may also be a bit nervous about having a small tuft of hair cut off. However, the amount of hair needed to measure cortisol is very small and the project staff will assure that the hair strands is cut from the back of the child's head in the least visible way. Some children may experience a mild discomfort from a "pinch" while having skinfolds measured and from lying down without moving during the bio impedance measurement. The study team members will do these measurements as quickly as possible to minimize the potential discomfort. The children will generally experience some discomfort during the cold pressor test due to the cold-related pain, but they are able to remove their hand at any time, and the pain mounts slowly and can be terminated before becoming severe. We will pay close attention to the reaction of the child and if the child experiences distress or displays other symptoms, we will terminate the procedure, comfort the child and call their parent.

#### **9.4.6 Results from cognitive tests**

The purpose of the assessments of cognitive function, behavior, and emotion is to describe variations within certain areas of cognition and behavior in healthy children in the two intervention groups. The tests will not be used to diagnose or make a general evaluation of the individual child. The personnel performing the measurements will be trained and supervised by a psychologist to assure the most comfortable and proper test environment for the children.

#### **9.4.7 Analysis of genetic material (GWAS)**

The blood stored in the research biobank will also be used for genome wide association studies (GWAS) analysis, analysis of single nucleotide polymorphisms and epigenetics. It is highly unlikely that the analyses will detect any serious inheritable genetic disposed illnesses. The genotype analyses will not include any full genome or exome sequencing, but will use a chip, that reveals information on common gene variants (>5%). It is therefore considered highly unlikely that we identify any genetic variants that have any direct relevance for illnesses.

#### **9.4.8 Serious unexpected adverse reactions or events:**

A serious adverse event is any untoward medical occurrence that:

- Results in death
- Is life-threatening at the time of the event;
- Requires inpatient hospitalization;
- Results in persistent or significant disability or incapacity.

The project responsible will immediately inform the committee if suspected unexpected serious adverse reactions or serious events occur during the project. The report will comment on any outcomes for the concerned trial. Reporting will take place no later than 7 days after the project responsible became aware of any such adverse reactions or events, as well as once yearly during the study together with an assessment of the safety of the study participant. The standard forms from the committee will be used for this purpose. In case of serious adverse reactions or serious events resulting from the project, the investigator will make available any information requested by the committee.

At the baseline visit parents will be made aware to contact us throughout the study period in case they experience any adverse events or reactions, and at the endpoint visit parents will be asked if they have experienced any adverse events or reactions. All adverse events and reactions will be registered and evaluated using a standard form from the Danish GCP unit (Appendix 21).

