#### **3.5.3 Procedure for exclusion and withdrawal**

A participant can be excluded from the study if the clinically responsible physician finds it advisable due to medical reasons. A participant can also be excluded for ethical reasons e.g. if the project staff and/or clinically responsible physician judges that the child does not want to continue his/her participation in the study, which will always be respected. Finally, a participant can be excluded if non-compliance with the procedures described in the information material is clearly demonstrated. Reasons for exclusion will be recorded and parents will be informed about the decision.

Parents will be informed that they can withdraw their child from participation at any time without giving a reason. At withdrawal we will ask the parents if they will tell us the reason for withdrawal. Responding is voluntary and we will not put pressure on the parents to make them respond.

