### **3.6 Recruitment of study participants**

A total of 150 children completing the study are needed. From our previous studies in children we expect a drop-out of up to 15-20%, and expect unsuccessful blood sampling in an additional 10% of the children at either baseline or endpoint. Therefore, a total of 200 participants will be recruited.

Boys and girls of the relevant age will be identified through the Danish Civil Registration System (CPR registry) and recruited via postal invitation letter to the parents (Appendix 2). Participants will mainly be recruited from the Capital Region of Denmark, but if necessary also from other parts of Zealand. Participants may also be recruited through advertisements in Danish newspapers, shared through networks and social media such as Facebook, and by notices in schools and after school clubs (Appendix 6). Parents that respond to the advertisements will receive the same information material as parents contacted through the CPR registry. The letter will contain a link to an electronic response form and the information material (Appendix 3). The brochure "The legal rights of study participants in a health science research project" [Forsøgspersonens rettigheder i et sundhedsvidenskabeligt forskningsprojekt], published by the Danish Committee on Biomedical Research Ethics system in August 2014, will be included in the information material.

Parents are asked to carefully read the material, if they wish together with a family member or a friend, and to explain the content to their child. Parents who return the response form will be called by telephone by the project staff. Here the participants will be pre-screened according to the inclusion and exclusion criteria. If they are still interested in participating, they will be invited to an information meeting where the study will be explained orally to parents and child by a project staff member who has been specifically trained for this task. Parents will be informed that they can bring an assessor (e.g. a family member or a friend) to the information meeting, if they wish so. If the participants do not fulfil the criteria for participation they will be informed hereof and will not be contacted or bothered further. Only one eligible child from each household can be included as a study participant, since for practical reasons individual randomization within a household is not possible.

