| Other                                     | 
 
• Child has breakfast
 
                                                                                                                                                                                                                                                                                                                                           |
| Cognitive function, behavior and emotions | 
 
• Tests, interviews and questionnaires
 
                                                                                                                                                                                                                                                                                                                          |
| Study foods                               | 
 
• Interview on dietary habits, preferences, and perceptions
 
• Instructions on intake and recording of study foods
 
• Receive first batch of study foods
 
                                                                                                                                                                                        |
| During the intervention (12 weeks) | 
 
• Collect study foods from NEXS (every 1-2 weeks)
 
• Cook and eat study foods
 
• Register intake of study foods
 
                                                                                                                                                                                                                                 |
| At home before endpoint visit      | 
 
• Fill out lifestyle questionnaire (Appendix 8)
 
• Fill out questionnaire on behavior, emotions, and cognitive function (Appendix 9-11)
 
• 4 days of dietary recording
 
• 7 days + 8 nights of physical activity and sleep recording (accelerometer)
 
• Apply EMLA patches to the child's forearms
 
• Overnight fasting
 
 |

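### Adverse events are actively asked about only at the endpoint visit; no equivalent question or form is fixed for children who withdraw or are excluded early

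*Protocol*

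**What the plan says.** Protocol section 9.4.8 sets two routes for collecting adverse events. The first is passive and open to every family: "At the baseline visit parents will be made aware to contact us throughout the study period in case they experience any adverse events or reactions". The second is active and happens once: "at the endpoint visit parents will be asked if they have experienced any adverse events or reactions". The same section says that all events are to be registered and evaluated on a standard form, Appendix 21.

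For children who leave early, section 3.5.3 states: "At withdrawal we will ask the parents if they will tell us the reason for withdrawal". Answering is voluntary. If the study team excludes a child, the reason is recorded. Section 7.2 adds that side effects which staff suspect or families report go to the responsible physician.

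Section 3.6 gives the planning figures. On attrition: "we expect a drop-out of up to 15-20" per cent. On blood sampling: "expect unsuccessful blood sampling in an additional 10% of the children at either baseline or endpoint". On the total: "Therefore, a total of 200 participants will be recruited".

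No section requires the adverse-event question or the Appendix 21 form at withdrawal or exclusion.

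**The concern.** The active question is attached to a visit that a child who leaves the study would not ordinarily attend. Completers have a direct question put to them. For early leavers the plan depends on a parent choosing to make contact, or on an event happening to be given as the reason for leaving. A reason for withdrawal is a narrower enquiry than a question about adverse events: it asks for a motive, and an event that was not the motive has no prompt.

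What is at stake is whether the safety data cover all randomised children evenly. Section 9.4.8 intends that every event be registered, and section 9.5 weighs the study's benefits against a very low risk of harm. Counts that are complete for those who stay and patchy for those who leave support that judgement less well. For completers, the active question also looks back over 12 ± 3 weeks (section 3.4), so up to 15 weeks. Parents know which food the child received (section 3.3).

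**Working it through.** **1. Reproduce the recruitment figure.** Inputs from section 3.6: 150 completers needed, drop-out of up to 15-20%, and a further 10% with failed blood sampling.

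- Losses added, 15% drop-out: 150 / (1 − 0.15 − 0.10) = 150 / 0.75 = 200. This is the protocol's figure.
- Losses multiplied, 15% drop-out: 150 / (0.85 × 0.90) = 196.1.
- At 20% drop-out: 150 / 0.70 = 214.3 (added) or 150 / (0.80 × 0.90) = 208.3 (multiplied).

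So 200 corresponds to the 15% end of the drop-out range.

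**2. Children outside the active question.** The number of early leavers is N × d.

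- 200 × 0.15 = 30
- 200 × 0.20 = 40

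That leaves 170 to 160 children whose parents would be asked. Since the protocol words its rate as an upper limit, 30 to 40 is a ceiling range. The 10% with failed blood sampling are counted separately from drop-out and are not added here.

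**3. Set the two groups side by side.**

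| Source of adverse-event information | Completers | Early leavers |
|---|---|---|
| Open invitation to report (9.4.8) | yes | yes |
| Physician review of suspected or reported side effects (7.2) | yes | yes, while in the study |
| Direct question about events (9.4.8) | yes, at endpoint | none fixed |
| Reason for leaving (3.5.3) | not applicable | voluntary at withdrawal; recorded at exclusion |

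The difference is in the third row. The fourth row offsets it only in part.

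**4. Illustration under assumption.** The documents give no event rates. Let m be the risk of an event in an early leaver relative to a completer. The share of children with events who fall outside the active question is d·m / [(1 − d) + d·m]; the underlying event rate cancels.

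- m = 1: 0.15 / 1.00 = 15% to 0.20 / 1.00 = 20%
- m = 2: 0.30 / 1.15 = 26% to 0.40 / 1.20 = 33%
- m = 3: 0.45 / 1.30 = 35% to 0.60 / 1.40 = 43%

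These are shares not actively asked about. They would be shares missed only if nothing at all were learned by the other routes, so they are upper limits on any loss, conditional on the assumed m and on drop-out at the protocol's upper figure.

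**The case against.** The strongest answer is that the protocol does not leave early leavers unheard. Every parent is invited to report throughout the study, families come to the site regularly (Table 1: "Collect study foods from NEXS (every 1-2 weeks"), suspected side effects go to the physician, and parents are asked why they are withdrawing. Passive reporting with one closing question is also a defensible choice for supermarket foods in children who must like both of them. Most of this stands, and it rules out several stronger readings that a reader might infer:

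- *That withdrawn children are never asked anything.* Section 3.5.3 asks for the reason. What is missing is a structured adverse-event question.
- *That harms are lost mainly in children who stopped because of them.* Those events are the likeliest to surface, because they would be the reason given. The weaker spot is events that were not the stated reason.
- *That a quarter to two fifths of events would be lost.* Those percentages rest on assumed relative risks and describe events not actively asked about.
- *That one arm's event rate will be understated.* This would need drop-out and reporting to differ by arm. The documents give no figure for either, and sections 5.1 and 5.2 describe no adverse-event comparison.
- *That Table 1 shows no enquiry at food collection.* Table 1 does not list the question at the endpoint visit either, where section 9.4.8 requires it, so its silence proves little.

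The protocol also does not say whether a child who stops the study food may still attend the endpoint visit. If such children attend, the number outside the active question falls.

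None of this supplies the missing step. A voluntary motive for leaving is not an adverse-event enquiry, and the form is not tied to withdrawal or exclusion.

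**Conclusion.** The point holds in a limited form. As written, the plan gives completers one active adverse-event question. For early leavers it gives spontaneous reporting plus a voluntary reason for withdrawal or a recorded reason for exclusion. Ascertainment is unequal for up to 30 to 40 of 200 children, assuming drop-out reaches the protocol's upper figure and early leavers do not attend the endpoint visit. Under-counting in this group is a plausible risk, mainly for events unrelated to the decision to stop. Its size cannot be derived from the documents, and no bias between arms is demonstrated. This is a minor but worthwhile improvement to safety data collection. It has no bearing on the primary outcomes or the power calculation.

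**What to change.** In sections 9.4.8 and 3.5.3, add that when a child withdraws or is excluded, parents are asked the same adverse-event question as at the endpoint visit, that answering is voluntary, and that any events are recorded on the Appendix 21 form. It would help to state in the same place whether a child who stops the study food may still attend the endpoint visit.

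Optionally, add one adverse-event line to the weekly record of study-food intake that parents already keep (section 4.5), to shorten recall. Asking in person at every food collection is more debatable, because it means repeated questioning for a small gain. How events are tabulated can be left to the statistical analysis plan.

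The cost of the main change is one extra question at a contact the protocol already foresees, and a few more minor events to register and evaluate. It adds no visits and leaves the sample size and power as they are.
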